### Intervention

The intervention study arms are:

Group 1—active intervention: targeting change in addictive eating behaviours using a multicomponent clinician-led approach (telehealth sessions, programme workbook and programme website).

Group 2—passive intervention: targeting change in addictive eating behaviours using a multicomponent self-guided approach (programme workbook and programme website).

Group 3—control dietary feedback, via paper-based report, provided at baseline, and participants follow their usual dietary pattern for 6 months.

The comparator groups were chosen to provide a passive delivery option of the programme, which would be consistent with a self-guided cognitive–behavioural therapy approach (group 2), and a control group consistent with a standard version of dietary feedback (group 3). The control group is not a wait list control; however, participants in this group will be offered access to the passive intervention (ie, programme workbook and programme website) after the completion of the 6-month assessment.

### TRACE active intervention (group 1)

Participants will receive five standardised one-on-one telehealth/phone sessions with an Accredited Practising Dietitian, with training in behaviour change and eating disorders, over a 3-month period (ie, weeks 1, 2, 4, 8 and 12). Additionally, dietitians leading the intervention delivery will have extensive experience in private practice work and working with clients including those with disordered eating and those with mental health conditions. Sessions will range from 15 to 45 min. Telehealth sessions will be provided via the VSee platform (www.vsee.com). The active intervention uses personalised feedback, skill-building exercises and goal setting to help individuals reduce their symptoms of addictive eating and improve their dietary intake and relationship with food (see table 2 for overview of intervention sessions). The intervention is personalised based on an individual’s dominant trait/s associated with personality and risk of addictive behaviour (ie, the traits: depression proneness, anxiety proneness, sensation proneness and/or impulsivity proneness; measured via the Substance Use Risk Profile Scale,^37^ which the individual scores the most highly for) and addresses a range of factors that influence behaviour, both internal and external. Further, dominant trait/s associated with personality and risk of addictive behaviour are mapped to specific coping skill strategies, which are in turn incorporated into the goal-setting process. As part of session 1, the first 15 min of the consultation will be audio recorded to enable qualitative analysis of responses to two standardised questions regarding the elements of ‘control’ and ‘compulsion’ around the participant’s food intake. These two themes were previously identified, through thematic analysis of the feasibility study data,^66^ as having an influential relationship with addictive eating behaviours. On completion of the five telehealth sessions, participants will be invited to join a closed Facebook group from 3 months post-commencement of the intervention until the 6-month outcome survey measures are conducted. Joining the Facebook group is voluntary.

**Table 2 T2:** Overview of intervention sessions

Session	Session aims
1. Personality (week 1: 45 min)	Introduce the intervention Determine participants’ main concerns with their food intake Provide feedback on baseline scores of addictive eating Discuss what this means when attempting and preparing to make changes Provide feedback on traits associated with personality and risk of addictive behaviour Discuss how personality traits may relate to food intake and addictive eating, and what this means for the individual Discuss coping strategies based on personality traits and complete ‘Urge Surfing’ activity Introduce ‘Distraction List’ Set homework task: choose and practice 2 coping strategy exercises Provide session summary
2. Food (week 2: 45 min)	Review session 1 Check in for episodes of overeating Discuss progress with homework task—coping strategies Provide feedback on dietary intake Discuss core versus non-core food intake (optional: discuss alcohol intake) Develop 3 nutrition goals using *SMARTER Goal Checklist* Positive—increase core foods Reduction—decrease non-core foods ‘Eating awareness’—using strategies to delay or halt overeating Discuss enablers/barriers when making changes to eating habits Discuss 'No Money No Time' website (www.nomoneynotime.com.au) Discuss ‘Practical Strategies to Achieve Goals’ Set homework task: complete ‘Triggers for Overeating Checklist’ Provide session summary
3. Skills (week 4: 30 min)	Review session 2 Assess progress with SMARTER goals Check in for episodes of overeating Discuss homework task—'Triggers for Overeating' Explore strategies to overcome triggers, building on previous coping strategies and ‘Practical Strategies to Achieve Goals’ Discuss and determine a ‘food line’ to identify when eating is no longer enjoyable or not tasting food Discuss strategies to stay below the ‘food line’ Set homework task: complete ‘Mood Monitor*’* worksheet Provide session summary
4. Confidence (week 8: 30 min)	Review session 3 Discuss progress with plan to stay below 'food line' and for episodes of overeating Explore enablers/barriers to achieving goals Discuss homework task—‘Mood Monitor’, and explore emotions that the participant has difficulty coping with Discuss seeing emotions differently Explore coping strategies for difficult emotions Discuss importance of sleep, physical activity and responsible intake of alcohol for emotional health Discuss implementing coping skills plan to achieve SMARTER goals (ie, consolidate information from sessions 1–4) Set homework task: practice implementation of coping skills plan to achieve goals Provide session summary
5. Moving forward (week 12: 20 min)	Review session 4 Check in/briefly problem solve and encourage participants to continue with goals and strategies Discuss topics from previous sessions (participant led) Reassess confidence to achieve goals Provide final *Addictive Eating Action Plan* Discuss how support group on Facebook works and encourage sign up

#### Participant workbook and programme website

Participants will have access to a participant workbook and password-protected access to a study-specific website, both built for the study to support the materials discussed in the intervention sessions. To further facilitate the co-design process, the workbook and website content were piloted with end users (n=2) with lived experience of addictive eating, who participated in the iKT interviews/workshops. The end users reported the workbook and website to be highly usable in terms of the content, and the language used throughout as appropriate with only minor modifications made. Additionally, the piloting process allowed the estimated time to complete each workbook module to be calculated.

#### Programme workbook

The workbook consists of five modules: (1) personality; (2) food; (3) skills; (4) confidence and (5) moving forward. The content of the five modules mirrors that of the telehealth sessions. The workbook also contains reflective activities/worksheets, discussed during the telehealth sessions, for the participants to complete. These elements were deemed important during the iKT process. The amount of time spent completing activities in the workbook each week, between telehealth sessions, will take approximately 30–60 min. However, the time to complete each module may vary from person to person, and participants are advised to work through the workbook at a pace that is right for them.

#### Programme website

The website includes the following pages: (1) home/landing page: brief information about the programme and login; (2) dashboard: navigation page to access each of the programme’s module pages; (3) module pages: each of the five modules within the intervention has a separate page on the website—this includes additional resources to complement the telehealth sessions and workbook; and (4) about us: brief information about the research/clinician team behind the programme, including contact information (email). The website will be available for a period of 12 months from study commencement. All data captured from the website will be encrypted and stored securely on a server.

#### Programme Facebook group

This is a voluntary part of the study, which aims to further support participants with behaviour change. The Facebook forum is set up as a private Facebook group. Participants can use their standard Facebook login, or alternatively, create a new login (a pseudo-account) that does not identify them if they wish to remain anonymous. Participants will be prompted with information related to the intervention for the 3-month duration in the form of short posts, blogs and polls. The Facebook group will allow participants to engage with other participants from the programme, as well as serve as a communication method to remind participants about assessments for the study.

The Facebook forum has the following restrictions: (1) membership will be by invitation only; (2) the group will not appear in search results or the participant’s Facebook profile; and (3) only group members will be able to see the group information and group posts. Participants will be advised of the appropriate use of language and etiquette for using the social media/discussion forum in the workbook and reminded at the final telehealth session. The Facebook group will be moderated by a member of the research team via the TRACE research Facebook account.

#### Intervention fidelity

A detailed clinician manual will be used by the dietitian for all telehealth sessions to maintain treatment fidelity. Dietitians administering the intervention will be trained by the principal investigator prior to study implementation. Dietitians will also follow each session as outlined in the manual and keep a dietitian log of participants’ telehealth sessions. Further, five participants allocated to group 1, with their consent, will have all their telehealth sessions audio recorded. The dietitian log and audio recordings will be reviewed by an independent researcher to ensure the intervention was delivered as intended. Regular supervisory meetings will be conducted with the dietitians and study coordinator led by the principal investigator. Participant adherence to the intervention will be assessed by a session attendance checklist completed by a member of the research team. Dietitians administering the telehealth sessions will monitor completion of homework tasks and workbook activities at the start of telehealth sessions 2–5. Assistance will be provided by the dietitian at this time if participants experienced any difficulties completing the homework tasks/activities. Additionally, to assist with adherence, on completion of each telehealth session, the dietitian will email a personalised ‘Addictive Eating Action Plan’, completed on a standardised template, to the participant.

### TRACE passive intervention (group 2)

Participants will receive the intervention via self-guided approach, with access to the five-module workbook and website (as described above), but without the telehealth consults. The content of the workbook modules mirrors the content of the five telehealth sessions. In addition to the written materials provided, the workbook contains spaces for reflective activities, documenting goals and monitoring progress. Participants will be asked, on receipt of the workbook, to complete the workbook within a 3-month period. The proportion of the workbook completed by participants in the passive intervention arm will not be monitored. Following the 3-month self-guided learning period, participants will be invited to join the closed Facebook group as described above.

### Control (group 3)

Participants will receive personalised dietary feedback on baseline surveys, provided by an automated report, generated from the Australian Eating Survey. This is consistent with standard dietary feedback from a dietitian. Participants in the control group will be offered access to the participant workbook and study website after the completion of the 6-month assessment.

### Patient and public involvement

Consumer (ie, individuals with lived experience of addictive eating who participated in the pilot study) input was received on the pilot version of the intervention (FoodFix process evaluation^24^) that directly guided the enhancement of the TRACE telehealth sessions. The TRACE Programme workbook and website for the current study were developed following the pilot study. A sample of consumer representatives (individuals with lived experience of addictive eating and healthcare experts including clinicians and managers), independent of those involved in the pilot study, were involved in the review of the programme and programme materials.^49^

Consumer representatives were interviewed to:

Identify what individuals with addictive eating need and want more accurately.Gather information about what works well and what needs improving, first hand from consumers who may use them.Openly consider different or opposing views about aspects of the research project.Test resources during development and refine resources making sure they will work well in practice.Detect any unforeseen consequences of a particular decision or direction that has been made regarding the project.Gain support of consumers to implement changes to the research project.

The opinion of consumers has been considered to create a programme that:

Aligns to the needs of the people it is trying to help, that is, individuals with addictive eating.Is beneficial in terms of delivering meaningful outcomes for individuals with addictive eating.Is conducted in a way that is sensitive to people’s needs.

Consumers were not involved in the design of the current study, the selection of outcome measurements, research questions or the recruitment of additional participants. However, consumers were involved in the overall concepts employed in the study and may be called upon at the dissemination stage. For example, to review plain language summaries of the results, provide advice on ways to communicate/translate our findings or present our findings to the community. Participants of the current study can request a plain English summary of the study outcomes on its completion.

### Outcome measures

All outcome measures are completed at baseline, 3 months (immediate post-active intervention period) and 6 months (follow-up) via online surveys. The same survey tools will be used at each time point. Participants will receive assessment reminders by email (reference to where data collection forms can be found is included in online supplemental material 2).

10.1136/bmjopen-2022-064151.supp2Supplementary data

### Primary outcomes

#### Addictive eating symptoms and severity

The YFAS 2.0^6^ will be used to assess the change in addictive eating symptomatology and severity. The YFAS 2.0 is a validated self-report 35-item questionnaire. The YFAS 2.0 asks participants to think of specific foods they have had difficulty controlling the consumption of within the past 3 months (eg, ice cream, chocolate, chips, hamburgers). The YFAS 2.0 provides an addictive eating symptom score ranging from 0 to 11. Additionally, two items assess clinically significant impairment or distress from eating. A ‘food addiction diagnosis’ can be given when ≥2 symptoms are endorsed, and clinically significant impairment or distress is present. However, for the purpose of this study, a ‘food addiction diagnosis’ will not be given, and severity of addictive eating will be classified in accordance with YFAS scoring instructions as follows: ‘mild’=3 symptoms, ‘moderate’=4–5 symptoms or ‘severe’=≥6 symptoms. The YFAS 2.0 has been found to be a robust and psychometrically sound measure of addictive eating symptomatology in non-clinical^2 67^ and clinical populations with good test/retest validity.^68^ Preliminary evidence^23 24^ suggests that YFAS scores are sensitive to change and are decreased after intervention.

### Secondary outcomes

#### Dietary intake and quality

Changes in dietary intake and quality will be measured using the Australian Eating Survey (AES).^69^ The following dietary outcomes will be measured: (1) core food and non-core food percentage contribution to total energy intake; (2) average daily energy intake, proportion of total energy intake contributed by macronutrient and micronutrient intake; and (3) overall diet quality. The AES is a validated 120-item semiquantitative Food Frequency Questionnaire that assesses usual food and nutrient intake over the previous 3–6 months. The AES includes a comprehensive list of foods, including drinks, milk and dairy foods, breads and cereals, sweet and savoury snacks, main meals, other foods, vegetables and fruits. Frequency response options for each food, or food type, range from ‘never’ to ‘≥7 times per day’. The AES has been assessed for comparative validity relative to weighed food records and for fruit and vegetable intake using plasma carotenoids.^69 70^ Standard portion sizes for adult men and women have been determined for each AES item in the survey, using data from the most recent Australian National Nutrition Survey. The food and beverage weight per serving, used in the calculation of food group servings (as serves per day), is consistent with sizes specified in the Australian Guide to Healthy Eating.^69–71^ Nutrient intake from the AES Food Frequency Questionnaire was computed using data in the AUSNUT 2011–2013 database.^72^ The AES also provides an Australian Recommended Food Score (ARFS), derived from a subset of 70 AES questions, as a measure of diet quality that reflects the overall healthiness and nutritional quality of an individual’s usual eating pattern.^70^ The ARFS is based on the frequency of consumption of core foods, recommended in the Australian Dietary Guidelines,^73^ with foods awarded 1 point for a consumption frequency of ≥once per week. The total score is calculated by summing the points for each item and scores can range from 0 to 73, with higher scores awarded for greater dietary variety.^70^

#### Depression, anxiety and stress

Changes in symptom scores for depression, anxiety and stress will be measured using the PHQ-8,^63^ the GAD-7^60^ and the Perceived Stress Scale (PSS-4),^61^ respectively. The PHQ-8 is a validated self-report eight-item tool that asks the individual to rate the severity of depressive symptoms over the past 2 weeks from 0 (‘not at all’) to 3 (‘nearly every day’). Total scores for the eight items range from 0 to 24, and severity will be determined using the following cut-offs: 0–4=minimal, 5–9=mild, 10–14=moderate, 15–19=moderately severe and 20–24=severe.^63^ The GAD-7 is a validated self-report seven-item tool that asks the individual to rate the severity of symptoms over the past 2 weeks from 0 (‘not at all sure’) to 3 (‘nearly every day’). GAD-7 total scores range from 0 to 21, and severity is determined using the following cut-offs: 0–5=mild, 6–10=moderate, 11–15=moderately severe and 16–21=severe.^60^ The PSS-4 is a validated self-report four-item tool that assesses the degree to which a person perceives life as stressful.^61^ The questions have been designed to assess how unpredictable, uncontrollable and overloaded a person feels their life to be. Frequency over the previous month is rated on a 5-point Likert scale ranging from ‘never’ to ‘very often’. PSS-4 total scores range from 0 to 16, and higher scores indicate greater stress.^61^ Currently, there is no established cut-off for the PSS-4 score to indicate adverse levels of stress.

### Other outcomes

A selection of other outcomes was chosen based on co-occurring health conditions (see table 1 for schedule of measurements).

#### Quality of life

Changes in subjective quality of life will be measured using the EQ-5D-5L.^74^ The EQ-5D-5L is a validated self-report five-item tool to assess health-related quality of life. It is a descriptive system comprising five dimensions: mobility, self-care, usual activities, pain/discomfort and anxiety/depression. Each dimension has three levels: no problems, some problems and extreme problems (labelled 1–3). Participants are asked to indicate their health state by ticking the box next to the most appropriate statement in each of the five dimensions. This decision results in a 1-digit number that expresses the level selected for that dimension. The digits for the five dimensions can be combined into a 5-digit number that describes the respondent’s health state. The EQ-5D-5L will be analysed to produce an index score between 0 (state of death) and 1 (perfect health).

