#### Cost analysis

A cost–consequence analysis will be conducted including calculating the cost of each intervention (ie, active, passive and control) and reporting intervention costs alongside mean change outcomes. Intervention costs will be recorded in terms of cost of intervention development, intervention delivery and the operating costs of the randomised controlled trial. Outcomes to be reported as part of the cost analysis will include mean change in addictive eating symptom scores assessed using the YFAS (ie, the primary outcome), as well as mean change in the number of healthcare appointments in the past 3 months assessed using the CSRI, and mean change in quality-adjusted life years assessed using the EQ-5D-5L. This approach was selected to provide a comprehensive and transparent overview of intervention costs, given the lack of cost analysis data in this area of research.^79 80^

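### The EQ-5D-5L is described with three levels, the QALY outcome is a change that is not defined, and trial operating costs are counted as intervention costs

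*Protocol article*

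**What the plan says.** Three statements in the protocol article matter here.

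- **Instrument (Other outcomes, Quality of life).** The measure is named: "Changes in subjective quality of life will be measured using the EQ-5D-5L". The dimensions are listed: "It is a descriptive system comprising five dimensions: mobility, self-care, usual activities, pain/discomfort and anxiety/depression". The response scale follows: "Each dimension has three levels: no problems, some problems and extreme problems (labelled 1–3". An index is then to be derived: "The EQ-5D-5L will be analysed to produce an index score between 0 (state of death) and 1 (perfect health". Table 1 also names the EQ-5D-5L and schedules it at baseline, 3 months and 6 months.
- **QALYs (Cost analysis).** One of the outcomes to be set beside cost is "mean change in quality-adjusted life years assessed using the EQ-5D-5L". It appears in the same list as the mean changes in YFAS symptom score and in number of healthcare appointments.
- **Costs (Cost analysis).** The analysis consists of "calculating the cost of each intervention (ie, active, passive and control) and reporting intervention costs alongside mean change outcomes". The cost components are then given: "Intervention costs will be recorded in terms of cost of intervention development, intervention delivery and the operating costs of the randomised controlled trial".

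Nothing elsewhere in the article corrects the response levels, says how QALYs are formed, or separates research costs from the cost of providing the programme.

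**The concern.** The cost–consequence analysis is announced in the abstract. The strengths and limitations box links it to implementation, and the closing Limitations section looks ahead to active and passive delivery as different levels of care in services. A reader would want three things from the resulting table: a correctly scored utility, a QALY figure that means what the term means, and a cost per arm that a service would face.

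As written, each is in doubt. The response coding belongs to a form other than the one named. The QALY outcome is phrased as a change from a baseline value that does not exist. The intervention cost includes spending that arises only because a trial is being run.

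**Working it through.** **1. Instrument.** Inputs: the name EQ-5D-5L, five listed dimensions, and three levels coded 1–3 (Quality of life section). The five dimensions account for the 5D in the name, so 5L is left to denote the levels. The number of health states is levels raised to the power of dimensions:

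- as described: 3^5 = 243
- as named: 5^5 = 3125
- 243 / 3125 = 7.8%

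The count of levels, the three labels and the 1–3 coding agree with one another and disagree with the name, so this is more than one mistyped digit. The text alone cannot show whether the description or the name is at fault.

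**2. QALYs.** Inputs: the index at 0, 3 and 6 months ("All outcome measures are completed at baseline, 3 months (immediate post-active intervention period) and 6 months (follow-up) via online surveys"). With index values u0, u3 and u6 and time in years, the area under the curve is

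QALY = 0.25 × (u0 + u3)/2 + 0.25 × (u3 + u6)/2 = 0.125·u0 + 0.25·u3 + 0.125·u6.

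The maximum over 6 months, with full health throughout, is 0.5. At baseline no time has elapsed, so there is no QALY total to subtract. Subtracting zero would credit a participant who stays at 0.70 throughout with 0.5 × 0.70 = 0.35, although nothing changed.

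The gain over staying flat at u0 is 0.25·(u3 − u0) + 0.125·(u6 − u0). The utilities below are assumed, since the article gives none:

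| Index at 0, 3, 6 months | Index change at 6 months | QALYs | Gain over flat 0.70 |
|---|---|---|---|
| 0.70, 0.80, 0.80 | 0.10 | 0.3875 | 0.0375 |
| 0.70, 0.75, 0.80 | 0.10 | 0.3750 | 0.0250 |
| 0.70, 0.70, 0.80 | 0.10 | 0.3625 | 0.0125 |
| 0.70, 0.80, 0.70 | 0.00 | 0.3750 | 0.0250 |

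For an index gain D at month 6, the first three rows give 0.375D, 0.25D and 0.125D. Index change is therefore 2.7, 4 or 8 times the QALY gain, depending on the path. In the fourth row it is zero while the QALY gain is positive. No constant converts one into the other.

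Baseline also matters when arms are compared. A chance difference δ in baseline index that simply persists adds 0.5δ to the difference in QALY totals, which is why adjustment for baseline index is needed.

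**3. Costs.** Let d_A and d_P be delivery cost per participant in the active and passive arms, and r the trial operating cost per participant, assumed equal across arms. The article plans equal allocation, the same survey schedule in every arm and the same maximum voucher total of $A60 per participant.

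- Reported cost per arm: d_A + r and d_P + r, each too high by r.
- Difference: (d_A + r) − (d_P + r) = d_A − d_P, unchanged.
- Ratio: (d_A + r)/(d_P + r), which moves towards 1 as r grows when d_A exceeds d_P.

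The article gives no cost figures, so r and its effect cannot be quantified.

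**The case against.** The strongest reply is that these are slips of wording in a condensed article. The EQ-5D-5L is named consistently in Table 1, Quality of life and Cost analysis, so an older description may simply have been carried over. A mean change in QALYs may be shorthand for index change or for incremental QALYs between arms. Recording costs by component is what allows them to be separated later, and the stated purpose is a transparent overview. Quality of life is an other outcome, and cost is not in the aim stated at the end of the Introduction.

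Much of this stands, and it rules out three stronger readings:

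- A reader might infer that the utilities will be wrong. The documents do not support that. If the five-level form was administered and scored as such, only one sentence is in error. The article names no value set and does not say that answers coded 1–3 will be scored as five-level answers.
- A reader might infer that the QALY gain will be overstated by some fixed factor. The article does not say that index change will be reported as QALYs, and the factor depends on the path; for a gain lost by month 6 the direction reverses.
- A reader might infer that shared research costs hide the cost gap between telehealth and self-guided delivery. If equal per participant, they cancel in the absolute difference. Only a ratio is compressed, and the article plans none.

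What does not stand is that this is merely detail left to a fuller plan. The three-level description is a positive statement that contradicts the instrument's name. The QALY outcome is specified in a form that has no meaning as written. The label of intervention cost explicitly takes in trial operation, with no commitment to report the components apart.

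**Conclusion.** The point holds as a correction to the quality-of-life and cost–consequence text.

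- The response scale contradicts the instrument's name. The consequence ranges from a wording change, if the 5L form was used, to a different instrument name and value set, if a three-level form was used.
- The QALY outcome needs a definition. Index change and QALY gain are not interchangeable: 0.125D to 0.375D QALYs for an index gain D at month 6. This assumes that the gain at month 3 lies between zero and D and that the index moves linearly between assessments.
- Counting trial operating costs as intervention costs raises every arm's figure above the cost of providing the programme. The absolute difference between arms is preserved if those costs are equal per participant. The size cannot be computed from the article.

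The primary YFAS analysis and the sample size do not use any of these quantities and are unaffected. The point is worth fixing before the cost analysis is run, but it does not threaten the trial's main conclusion.

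**What to change.** - **Instrument.** Confirm which EQ-5D form was in the survey, correct the description of levels and coding to match, and score with that version's coding and value set. Recruitment is reported as complete in April 2022, so the scoring must follow the form actually given at baseline.
- **QALYs.** Compute QALYs per participant as the area under the index at 0, 3 and 6 months, and compare arms adjusted for baseline index. Alternatively, report change in the index and call it that.
- **Costs.** Report delivery cost per participant as the intervention cost. Show one-off development costs and research-only costs on separate lines.

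The cost is a few sentences of text and minor analysis work. The index is already scheduled at all three time points and costs are already to be recorded by component, so no new data collection should be needed.
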